# Low-dose capecitabine adjuvant chemotherapy in elderly stage II/III colorectal cancer patients (LC-ACEC): study protocol for a randomized controlled trial

**DOI:** 10.1186/s13063-015-0753-7

**Published:** 2015-05-29

**Keywords:** Elderly, Colorectal cancer, Adjuvant chemotherapy, Capecitabine, Low-dose, Non-inferiority, Randomized controlled trial

## Abstract

**Background:**

Over half of the patients were diagnosed with colorectal cancer after 70 years of age. The choice of the most suitable chemotherapy strategy is the major challenge for elderly patients. Previous trials indicated that elderly patients with stage II/III colorectal cancer obtained no significant benefits from oxaliplatin-based adjuvant chemotherapy. Therefore, single-agent oral capecitabine is regarded as an effective alternative with retained efficacy and improved flexibility. However, the optimal dose of capecitabine for elderly patients remains controversial. Recent studies have adopted a low-dose strategy (1,000 mg/m^2^) for elderly patients, but the long-term efficacy of this strategy has not been identified so far. Thus, we designed this trial to investigate non-inferiority of the lower-dose strategy of capecitabine compared with the approved-dose strategy for adjuvant chemotherapy of elderly patients with stage II/III colorectal cancer.

**Methods:**

LC-ACEC (Low-dose Capecitabine Adjuvant Chemotherapy for Elderly Patients With Stage II/III Colorectal Cancer) is a prospective, randomized, open-label, non-inferiority phase III clinical trial including 926 eligible patients. Patients will be randomly assigned to receive a capecitabine adjuvant chemotherapy strategy of lower dose (1,000 mg/m^2^ twice daily on days 1 to 14 of every 21 days) or approved dose (1,250 mg/m^2^ twice daily on days 1 to 14 of every 21 days). The primary outcome is 3-year disease-free survival. Secondary outcomes include 3-year overall survival, toxic and side effects during treatment, completion rate, and quality of life.

**Discussion:**

This is the first randomized trial to evaluate the efficacy and safety of a low-dose strategy of capecitabine in adjuvant chemotherapy of elderly patients with stage II/III colorectal cancer, and the results are believed to provide new evidence on the treatment of elderly patients with colorectal cancer.

**Trial registration:**

ClinicalTrials.gov identifier NCT02316535 (Dec. 12, 2014).

## Background

In Western countries, the incidence of colorectal cancer (CRC) peaked in patients more than 70 years old [1]. As for Chinese patients with CRC, the median age of diagnosis was 50 in the 1980s; however, it had reached 58 in 2005 and has been rising recently [2]. Limited by age-related organ function decline and comorbid conditions, elderly patients show impaired physical and mental tolerance for cancer treatment, such as chemotherapy.

Generally, stage II (T_3-4_N_0_M_0_) and stage III (T_any_N_1-2_ M_0_) colorectal carcinoma, the most common CRC in Chinese patients [3], can be resected by surgery. Additional adjuvant chemotherapy could significantly improve survival of stage II/III CRC patients compared with surgery alone [4]. Results of a pooled analysis including 3,351 CRC cases indicated that, in view of both efficacy and safety, elderly patients (more than 70 years old) achieved the same benefits from adjuvant chemotherapy as younger patients [5]. According to the large-scale retrospective analysis of the Adjuvant Colon Cancer Endpoints (ACCENT) database, patients at least 70 years of age accounted for only 17.1 % of all cases [6], which was much lower than expected. Therefore, improving the acceptance and completion rate of adjuvant chemotherapy for elderly patients with stage II/III CRC has become imperative.

The oxaliplatin-based combination chemotherapy (Folfox, Xelox) has been widely recommended recently [7]. However, the ACCENT analysis reported that adding oxaliplatin extended no significant benefits for elderly patients [6], suggesting that single-agent chemotherapy might be preferred for those patients. Capecitabine (Xeloda; Hoffmann-La Roche Inc., Nutley, NJ, USA), as the oral prodrug of 5-fluorouracil (Fu) recommended by global guidelines [8–10], has been proven to be at least equivalent to Fu bolus and intravenous Fu plus leucovorin (Lv) adjuvant chemotherapy for CRC [11–13] and to haveenhanced flexibility and compliance [12, 14]. Currently, the approved dose of capecitabine is 1,250 mg/m^2^ twice a day (bid) on days 1 to 14 of every 21 days [15], but the optimal dose for various groups of patients characterized by different ethnicity and age remains controversial. Moreover, although only relatively healthy elderly patients—that is, age of not more than 75 years and Eastern Cooperative Oncology Group (ECOG) performance status (PS) of not more than 1—were eventually included, the X-ACT (Xeloda in Adjuvant Colon Cancer Therapy) trial (m66001) found that 51 % of those patients undergoing 1,250 mg/m^2^ strategy required dose reduction to complete the whole chemotherapy, significantly more than younger patients, indicating that the approved dosage might be an overdose for elderly patients [16]. A previous non-randomized comparative analysis by Bajetta *et al*. reported that the completion rate (with no dose reduction) of a low-dose strategy of capecitabine (1,000 mg/m^2^ bid) was higher than the approved strategy (95 % versus 70 %), further concluding that 1,000 mg/m^2^ could be applied as a new recommended strategy for elderly patients with breast cancer [17]. The AVEX (bevacizumab plus capecitabine versus capecitabine alone in elderly patients with previously untreated metastatic colorectal cancer) trial (ClinicalTrials.gov identifier NCT00484939) in 2013 adopted the 1,000 mg/m^2^ low-dose strategy for metastatic CRC patients at least 70 years old [18]. However, it is well established that patients of different tumor stage have significantly different clinical characteristics. A recent single-arm study has verified feasibility of this starting dose at 1,000 mg/m^2^ bid for elderly (at least 70 years old) patients with stage II/III colon cancer [19] but has not produced results of efficacy. Thus far, however, no data on the optimal dose of capecitabine applied in elderly patients with stage II/III CRC have been available. Furthermore, the long-term efficacy of this 1,000 mg/m^2^ strategy, though widely used in elderly patients with cancer, has not been identified in comparison with the approved strategy.

For more individualized evidence guiding CRC treatment, we designed a non-inferiority randomized trial to identify the efficacy and safety of the low-dose capecitabine strategy (1,000 mg/m^2^ bid) for adjuvant chemotherapy of elderly (at least 70 years old) patients with stage II/III CRC.

## Methods

### Study objective

The primary objective of the LC-ACEC (Low-dose Capecitabine Adjuvant Chemotherapy for Elderly Patients With Stage II/III Colorectal Cancer) trial is to investigate the non-inferiority of the efficacy of low-dose capecitabine (1,000 mg/m^2^ bid) applied in adjuvant mono-chemotherapy for elderly patients with stage II/III CRC. Furthermore, we aim to compare the toxic and side effects, completion rate, and quality of life (QoL) of the low-dose strategy with the approved-dose strategy (1,250 mg/m^2^ bid).

### Study design and setting

This is a prospective, randomized, open-label, non-inferiority phase III clinical trial with two parallel groups. Patients in the low-dose group receive 1,000 mg/m^2^ bid capecitabine postoperatively; accordingly, patients in the approved-dose group receive 1,250 mg/m^2^ bid capecitabine. Fig. 1 illustrates the overall flow of participants in this trial.

**Fig. 1 Fig1:**
[figure not shown]
Overall flowchart of the LC-ACEC (Low-dose Capecitabine Adjuvant Chemotherapy for Elderly Patients With Stage II/III Colorectal Cancer) trial

Our trial began in January 2015 in the West China Hospital (WCH) of Sichuan University in China and is expected to end in 2023.

### Ethical considerations

This trial protocol is approved by the Biological and Medical Ethics Committee of WCH (reviewed in 2014 as #74) and has been registered at ClinicalTrials.gov (identifier NCT02316535). All of the eligible participants and their legal surrogates will be fully informed of potential risks and benefits of interventions in each group; only patients who are willing to provide written informed consent can be enrolled in the trial. The results of the trial will be reported in accordance with the CONSORT (Consolidated Standards of Reporting Trials) statement.

### Study population

The selection criteria of our trial are as follows:

#### Inclusion criteria

 With written informed consent Pathologically identified carcinoma of colon and rectum pT3-4NanyM0 or pTanyN + M0 (stage II/III) Age of at least 70 years to not more than 90 years Underwent R0 resection (that is, no residue tumor) ECOG PS of not more than 2 Life expectancy of at least 3 months Initiation of adjuvant therapy within 12 weeks after surgery [20].

#### Exclusion criteria

 With other types of malignances within the past 5 years Creatinine clearance of not more than 50 mL/minute History of neoadjuvant chemotherapy In anticoagulant therapy History of angina pectoris, congestive heart failure, or myocardial infarction within the past 12 months History of other antineoplastic drugs History of substance abuse With other contraindications for chemotherapy (for example, thrombocytopenia, ongoing infection, and impaired liver function).

### Randomization and blinding

All participants fulfilling the inclusion criteria will be randomly allocated into either the low-dose or the approved-dose group. We use a computer-generated blocked randomization sequence with the block size of four according to the previous published trial conducted in WCH [21]. Patients are randomly assigned by stratification of disease stage (stage II or III) and primary tumor site (colon or rectum). To achieve allocation concealment, opaque envelopes with sequential numbers are adopted to seal the assignment and are accessible only for investigators not involved with this trial. After enrollment of each patient, the envelope is sent to an independent investigator, who is not involved in patient evaluation, to assign participants to either the low-dose or the approved-dose group. This is an open-label trial; thus, patients, investigators, and data analysts are aware of the group assignment.

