#### Sample size and statistics

The LC-ACEC trial aims to identify the non-inferiority of 3-year DFS of patients in the low-dose capecitabine adjuvant chemotherapy group versus the approved-dose group. We assumed that a background 3-year DFS was 60 % and predefined the non-inferiority margin of the hazard ratio (HR) as 1.30. When 456 events of the primary endpoint 3-year DFS occur, the efficacy analysis will be conducted. We chose a statistical power of 0.80 and a significance level of 0.05 (two-sided). Given the 10 % drop-out for elderly patients, the calculation yielded a sample size of 926 patients (463 in each arm) [11, 25].

The intention-to-treat analysis will be applied with all patients who undergo randomization in this trial. With regard to survival data, HRs with 95 % confidence intervals (CIs) will be presented by Kaplan-Meier survival estimates. Additionally, Cox proportional HRs with 95 % CIs will be calculated on the basis of subgroups of different characteristics (that is, age, sex, stratum, and Charlson comorbidity index), which can identify the influence of competing risk factors for the outcome event. For the primary outcome of 3-year DFS, the non-inferiority will be concluded if the upper limit of the 95 % CI is not more than 1.30 (predefined non-inferiority margin). As for other outcomes, proportions will be compared by using chi-squared test, and continuous data will be analyzed by *t* test. All the statistical analyses will be conducted by using SPSS version 20 software (SPSS, Inc., Chicago, IL, USA).

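### A fixed, published block size of four with open assignments would let a recruiter who tracks each stratum deduce up to one third of allocations, which weakens concealment

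*Protocol article*

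**What the plan says.** All quotations are from the protocol article.

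- **Sequence** (Randomization and blinding): "We use a computer-generated blocked randomization sequence with the block size of four according to the previous published trial conducted in WCH". The section mentions no other size, and does not say that the size varies or is kept from recruiting staff.
- **Strata** (same section): "Patients are randomly assigned by stratification of disease stage (stage II or III) and primary tumor site (colon or rectum". This makes 2 × 2 = 4 strata. Eligibility rests on pathology after resection, so both factors are known before enrolment.
- **Blinding** (same section): "This is an open-label trial; thus, patients, investigators, and data analysts are aware of the group assignment".
- **Concealment** (same section): "opaque envelopes with sequential numbers are adopted to seal the assignment and are accessible only for investigators not involved with this trial". After enrolment, "the envelope is sent to an independent investigator, who is not involved in patient evaluation", and that person makes the assignment.
- **Setting** (text under Fig. 1): "Our trial began in January 2015 in the West China Hospital (WCH) of Sichuan University in China". No other hospital is named.
- **Allocation ratio** (Sample size and statistics): "the calculation yielded a sample size of 926 patients (463 in each arm", so the arms are equal.

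**The concern.** Concealment has two parts: nobody recruiting may read the next assignment, and nobody may work it out. The envelopes and the independent assigner deal with the first. The second depends on the sequence being unpredictable. A single small block size, stated publicly and combined with visible past assignments, makes part of the sequence predictable.

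The article itself gives reasons why a clinician might act on a prediction. The Background suggests that the approved dose may be too much for elderly patients, while the Discussion warns that reducing the dose may cost efficacy, so preferences could run either way. There is also room to act. Adjuvant treatment may start up to 12 weeks after surgery, eligibility spans ages 70 to 90 and ECOG performance status up to 2, and the exclusion for other contraindications leaves some judgement to the recruiter.

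At stake is the prognostic balance of the arms, and with it the hazard ratio (HR) for disease-free survival, the completion rate and toxicity. The intention-to-treat analysis does not protect against selection that happens before randomization.

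**Working it through.** The plan gives no figure for predictability, so there is none to reproduce.

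**Inputs.** Block size 4, open assignments and four strata come from Randomization and blinding. The total of 926, with 463 per arm, comes from Sample size and statistics. Two assumptions are added: each block holds two patients per arm (inferred from the equal arms), and blocks run separately within each stratum.

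**Step 1: allocations known with certainty.** There are six equally likely blocks: AABB, BBAA, ABAB, ABBA, BAAB and BABA. Together they hold 6 × 4 = 24 places. A place is forced once one arm has used both of its places.
- Fourth place: always forced, 6 places.
- Third place: forced when the first two match (AABB and BBAA), 2 places.
- Total: 8/24 = 33.3%. Applied to 926 patients, 926/3 = 308.7, or about 309.

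A simulation of 926 patients over four equal strata, each tracked separately, gives 33.2%.

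**Step 2: best guess.** The rule is to guess the arm that is behind and to toss a coin when the arms are level. The chance of being right at places 1 to 4 is 1/2, 2/3, 2/3 and 1. The mean is (0.500 + 0.667 + 0.667 + 1)/4 = 2.833/4 = 70.8%, against 50% by chance.

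**Step 3: how far this depends on tracking.** In the same simulation, a recruiter who keeps only an overall tally and ignores strata is certain of no allocation and guesses right about 61% of the time. The share known with certainty therefore runs from 0 to 33%, depending on the records kept.

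**Step 4: what varying the block size changes.** The recruiter is assumed to know the set of sizes, but not which one is in use, and to track the stratum optimally.

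| Block sizes | Known with certainty | Best guess right |
|---|---|---|
| 4, fixed and known | 33% | 71% |
| 6, fixed and known | 25% | 68% |
| 8, fixed and known | 20% | 67% |
| 4 or 6 at random | about 6% | about 69% |
| 4, 6 or 8 at random | about 2% | about 68% |

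The fixed-size rows are exact enumerations. The random-size rows are simulated with the sizes equally likely. The last best-guess figure can be checked by hand: expected correct guesses per block are 2.833, 4.100 and 5.329 for sizes 4, 6 and 8, so 12.262/18 = 68.1%. It hardly moves because the arms return to balance at the end of every block, whatever its size.

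**Step 5: how much room the primary analysis has.** At 456 events the standard error of log HR is about 2/√456 = 0.0937. The upper 95% limit stays at or below 1.30 if the observed HR is at most 1.30/exp(1.96 × 0.0937) = 1.30/1.20 = 1.08. This shows how small a shift in the HR would matter. It does not estimate the shift that selection would cause.

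**The case against.** The strongest reply is that the trial has real safeguards: a computer-generated sequence, numbered opaque envelopes held outside the trial team, and an independent person who assigns only after enrolment. A reader might infer from the fixed block that concealment is defeated. The documents do not support that. The next assignment cannot be read, and two thirds of allocations cannot be known in advance even by a recruiter who tracks perfectly. What the safeguards leave open is deduction from earlier assignments before the decision to enrol.

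A reader might also take about 309 patients as the number whose allocation was foreseen. That figure is a ceiling. It needs an ordered record in all four strata and knowledge of where each block begins. The article does not show that anyone keeps such a record or sees every assignment.

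Nor do the documents support reading this as a bias towards non-inferiority. A recruiter who steered frail patients away from the approved dose by timing enrolment would load the low-dose arm with worse prognoses and make non-inferiority harder to show. Withholding frail patients from the trial, or holding the opposite preference, could act the other way. No effect on the HR has been demonstrated.

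Finally, it would be too absolute to say that nothing can be done at analysis. Measured imbalance can be examined and adjusted for, and the article already plans Cox analyses by age, sex, stratum and comorbidity index, though as subgroups. Unmeasured frailty would remain.

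These points limit the size and wording of the concern. They do not remove it.

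**Conclusion.** The point stands as an avoidable weakness in a stated procedure. With one published block size of four and open assignments, up to one third of allocations (8 of 24 places) can be deduced with certainty by someone who tracks each stratum. Concealment is weakened, fully so for that third and partly for the rest. The trial is exposed to selection bias of unknown direction and size, which analysis can correct only in part.

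The conclusion assumes 2:2 blocks within strata and a recruiting team able to see past assignments in order. The latter is plausible because only one hospital is named, but the article does not call the trial single-centre.

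**What to change.** For all patients still to be enrolled, have the independent holder of the list generate a new sequence within each of the four strata, using permuted blocks whose size varies at random (for example 4, 6 and 8). Do not disclose the sizes to recruiting staff, and amend the block-size sentence in Randomization and blinding accordingly. Under Trial status the article says recruitment is under way, so the change can still take effect. It does nothing for patients already randomized.

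Certain allocations among the remaining patients would fall from 33% to about 2%. Best-guess accuracy would fall only from about 71% to about 68%, so the change should be justified by the removal of certainty and not presented as making allocation unpredictable.

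The cost is a new computer-generated list, a new set of envelopes, and a slightly larger possible imbalance within a stratum. An incomplete block of 8 can leave a difference of up to 4, and a block of four cut short at the switch can add up to 2, so 4 + 2 = 6 at most. At present an incomplete block of four can leave a difference of at most 2.

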### Intervention

About 4 to 8 weeks after surgery [20], patients in the low-dose group will take oral capecitabine after breakfast and dinner at the dose of 1,000 mg/m^2^ bid, and patients in the approved-dose group will receive the dose of 1,250 mg/m^2^ bid. Each treatment cycle consists of 14 days of capecitabine administration and then 7 days of rest.

Colon cancer patients in both groups are supposed to take eight circles of treatment in total (24 weeks) [22]. Eight circles of treatment will also apply to rectal cancer patients who had neoadjuvant radiotherapy (regimen 1 in Fig. 2). For rectal cancer patients without neoadjuvant radiotherapy, we defined high-risk patients who need concomitant radiochemotherapy (RCT) as patients with positive circumferential resection margin (CRM+) or with lymph node metastasis (N+), and they will receive a total of five circles of chemotherapy [13]. The RCT serves as the third circle and lasts about 6 weeks [13]. During the RCT period, the irradiation dose is 45 Gy/25 fractions, and the capecitabine dose is reduced to 800 mg/m^2^ bid [23] (regimen 2 in Fig. 2). According to the toxic events, the dose of capecitabine will be adjusted following the drug instruction of Xeloda® [15]. Any patients who have intolerable toxic or side effects will discontinue the medication.

**Fig. 2 Fig2:**
[figure not shown]
Treatment regimen. RCT, radiochemotherapy

### Outcomes

#### Primary outcome

The primary outcome of the LC-ACEC trial is 3-year disease-free survival (DFS), which is calculated from the date of randomization to whichever of the following events occurs first in 3 years: local recurrence, metastasis, death from any causes, or development of other malignances.

#### Secondary outcome

Several secondary outcomes are adopted in this trial. In addition to the primary outcome of 3-year DFS, the 3-year overall survival is calculated from the randomization to the date of death from any causes. Toxic and side effects during adjuvant chemotherapy will be closely observed and evaluated by using National Cancer Institute Common Toxicity Criteria (NCI-CTC) version 2.0. Based on the toxic and side effects, we will keep every record of modification or discontinuance of capecitabine and calculate the completion rate of the treatment as one of the key secondary outcomes. Moreover, QoL data are recorded by using a Chinese translation of European Organisation for Research and Treatment of Cancer Core QoL Questionnaire C30 (EORTC QLQ-C30) [24].

#### Follow-up and data collection

The medical history and physical examination will be taken immediately at the outpatient clinic. After patients pass the selection procedure and sign the informed consent form, a series of investigations, including complete blood test (for example, blood cell count and blood chemistry), tumor markers of carcinoembryonic antigen (CEA) and carbohydrate antigen 19-9 (CA 19-9), total abdominal computed tomography (CT) scan, and chest radiograph, will be scheduled. It is worth mentioning that before every circle of chemotherapy, renal function of each participant will be monitored and evaluated by calculating the creatinine clearance. When participants finish every circle of chemotherapy, investigators will assess the toxic and side effects by using NCI-CTC and record any modification or discontinuation of capecitabine. In view of possible compromised compliance of elderly patients, returned medication will be checked at the clinic, and patients who discontinue the treatment for more than 1 week (except for toxic effects) will be withdrawn from this trial. When the whole treatment is over, patients will come to the hospital for a check-up every 3 months in the first 2 years and every 6 months afterward. Each time, the complete blood test, tumor markers, total abdominal CT scan, chest radiograph, and rectal examination will be conducted to help oncologists verify the possible local recurrence and metastasis, and the QoL questionnaire will be filled. We will follow up patients on a corresponding timeline at the clinic or by phone. All the data of each patient will be recorded in a case report form (CRF) in time.

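### Withdrawing non-toxic stoppers from the trial, not only from treatment, conflicts in substance with intention to treat and could bias the DFS hazard ratio in either direction

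*Protocol article*

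**What the plan says.** All references are to the protocol article.

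- **Follow-up and data collection**: "patients who discontinue the treatment for more than 1 week (except for toxic effects) will be withdrawn from this trial". What the patient leaves is the trial, not the drug. The sentence opens by expecting imperfect compliance in elderly patients.
- **Intervention**: the wording for toxicity is different: "Any patients who have intolerable toxic or side effects will discontinue the medication". Nothing there takes the patient out of the trial.
- **Sample size and statistics**: "The intention-to-treat analysis will be applied with all patients who undergo randomization in this trial". Non-inferiority is concluded if the upper 95% confidence limit of the DFS HR is not above 1.30. A 10% drop-out allowance is built into the 926 patients.
- **Primary outcome**: DFS is "calculated from the date of randomization to whichever of the following events occurs first in 3 years", so the endpoint runs far beyond the 24 weeks of treatment.
- **Follow-up and data collection**, later in the same paragraph: visits are scheduled once the whole treatment is over, and "We will follow up patients on a corresponding timeline at the clinic or by phone". Withdrawn patients are not mentioned.

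**The concern.** A patient who leaves the trial during treatment supplies no later recurrence or death data. In a time-to-event analysis such a patient can only be censored, at a point fixed by something that happened after randomization. Stopping for a non-toxic reason may go with frailty, early relapse or poor adherence, all of which bear on DFS.

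Three features of this trial make that matter:

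- The claim is non-inferiority. If poor-prognosis patients are lost mainly from the low-dose arm, the HR moves towards the claim.
- The trial is open-label (Randomization and blinding). Whether a stop counts as toxic or non-toxic decides who leaves, and that judgement is made with the arm known.
- The arms differ in dose and are expected to differ in tolerability, so the mix of toxic and non-toxic stops may differ by arm.

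The analysis plan cannot repair this later, because it cannot recover events that nobody collected.

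**Working it through.** **Reproducing the plan's figure.** The article states: "We assumed that a background 3-year DFS was 60 % and predefined the non-inferiority margin of the hazard ratio (HR) as 1.30". Power is 0.80 and alpha 0.05 two-sided. With 1:1 allocation and true HR 1.0, Schoenfeld's formula gives

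events = 4 × (1.960 + 0.842)² / (ln 1.30)² = 456.1,

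which matches the planned 456. The figure is not in dispute.

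**Effect of the rule on the HR.** The article gives no withdrawal rate and no prognosis for those withdrawn, so both are assumed. Set-up:

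- 463 patients per arm, exponential DFS, approved-dose 3-year DFS of 60%.
- Withdrawn patients censored at a uniform time in months 0 to 6.
- Every other patient followed for 4.65 years. With λ = −ln(0.60)/3 = 0.170 per year, this is the time at which 926 × 0.90 = 833 patients yield 456 events: −ln(1 − 456/833)/λ = 4.65.
- Cox HR with 95% CI, 1,500 runs per row. The same patients are analysed with full follow-up and with censoring at withdrawal.

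| Withdrawn, low v approved | Hazard if withdrawn | Dose HR put in | HR, full | HR, censored | Non-inferiority, full | Non-inferiority, censored | Events, full to censored |
|---|---|---|---|---|---|---|---|
| 15% v 5% | ×2 | 1.20 | 1.286 | 1.212 | 3.9% | 12.3% | 547 to 479 |
| 15% v 5% | ×2 | 1.25 | 1.337 | 1.263 | 1.1% | 5.5% | 553 to 485 |
| 5% v 15% | ×2 | 1.20 | 1.109 | 1.187 | 45.9% | 14.9% | 521 to 457 |
| 15% v 5% | ×1 | 1.25 | 1.244 | 1.245 | 6.9% | 6.2% | 544 to 492 |
| 10% v 10% | ×2 | 1.30 | 1.296 | 1.303 | 2.9% | 2.7% | 548 to 481 |
| 10% v 10% | ×1 | 1.30 | 1.299 | 1.301 | 3.3% | 3.5% | 550 to 500 |
| 10% v 10% | ×2 | 1.00 | 1.004 | 1.003 | 82.0% | 75.9% | 504 to 439 |
| 10% v 10% | ×1 | 1.00 | 0.998 | 0.999 | 84.2% | 80.5% | 506 to 459 |

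The extra hazard falls on withdrawn patients only, so an imbalance also moves the full-follow-up HR away from the dose HR put in. The full-follow-up HR is the intention-to-treat quantity.

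A second simulation with 4 years' accrual plus 3 years' follow-up (also assumed) gave 3.6% rising to 13.3% at a full-follow-up HR of 1.28. That agrees with the first row.

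The HRs of 1.28 and 1.29 lie just inside the margin, so those claims are false only in the loose sense of being at its edge. The 1.337 row lies strictly outside it, and there claims rise from 1.1% to 5.5%, above the 2.5% that the rule allows at exactly 1.30.

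**Effect on events.** The article says: "When 456 events of the primary endpoint 3-year DFS occur, the efficacy analysis will be conducted". If the HR is unbiased, power at the trigger is Φ(√456/2 × ln 1.30 − 1.960) = Φ(0.841) = 0.80, whichever patients supply the events. The lower percentages in the last two rows arise because follow-up is fixed at 4.65 years. Under the stated trigger, lost events mean a later analysis.

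**The case against.** **Loss of follow-up is inferred.** The article never says that DFS or survival follow-up stops, and its general follow-up sentence excludes nobody. A condensed article may leave data collection after withdrawal to the full protocol. A withdrawn patient censored in the assigned arm is also still formally in the intention-to-treat set. This stands in part. The article does not state the loss word for word, and the conflict is one of substance, not a flat contradiction. But leaving the trial is what the sentence says, the contrast with the toxicity wording supports that reading, and the scheduled visits begin only after treatment is complete. This is a stated rule at odds with another stated rule, not an omitted detail.

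**The bias has no known direction.** A reader might infer that the rule favours the low dose. The article does not support that. Toxicity, the obvious arm-related cause of stopping, is exempt. The one comparative completion figure cited in the Background (95% v 70%, breast cancer, non-randomized) favours the low dose. With the imbalance reversed, the rule works against non-inferiority. This stands in full.

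**Away from the margin the effect is small or harmless.** Under the same 15% v 5% assumption, a full-follow-up HR of 1.38 falls to about 1.31, and claims rise only from 0.3% to 2.1%, still below 2.5%. Where the dose itself has no effect, claims rise from about 60% to 79%, but the full-follow-up HR of 1.08 is inside the margin, so those claims are correct. This stands: the harm is concentrated near the margin.

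**Power.** A reader might infer that the trial falls below 80% power. The event trigger prevents that. For example, losing 60 of 540-580 events leaves 480-520, at which Schoenfeld power is about 82-85%. Waiting makes up lost events only if the trigger stays reachable. If events after 3 years did not count, 926 × 0.40 = 370 events would be expected at the assumed rate, which is a separate question about the endpoint.

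**Existing safeguards.** The 10% drop-out allowance enlarges the sample but does not correct selective loss. The monitoring board's review of drop-outs can show an imbalance but cannot restore outcomes.

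**Conclusion.** The point holds in this form: read plainly, the withdrawal rule ends DFS follow-up for non-toxic stoppers and defeats in substance the promised analysis of all randomized patients.

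Bias requires withdrawal that is both imbalanced and related to prognosis, and it can then go either way. With 15% v 5% and a doubled hazard, non-inferiority claims at the edge of the margin rise from about 4% to 12-13%. The opposite imbalance at a full-follow-up HR of 1.11 cuts them from 46% to 15%. Without imbalance, or without a link to prognosis, the HR is essentially unbiased and the main cost is a later analysis.

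These sizes rest on assumed rates and hazards and illustrate what could happen; they do not predict it. The article does not support the stronger readings that the rule will hide inferiority, that it favours the low dose, or that it leaves the trial underpowered. The case for change does not need them: the direction cannot be known in advance, and uncollected outcomes may not be recoverable.

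**What to change.** Reconcile the two sections by changing the end of the withdrawal sentence to, for example: *are recorded as having discontinued study treatment, remain on the scheduled clinic or telephone follow-up for DFS and survival, and are analysed in their randomized arm; data collection ends only if the patient withdraws consent to follow-up.* The rule on when treatment stops is left as it is.

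The cost is one protocol sentence and a case report form field that separates stopping treatment from leaving the study, with the reason and date. Follow-up uses visits and calls that the article already schedules. Recruitment was under way at publication, so the change should be made early and, where consent allows, follow-up resumed for anyone already withdrawn under the rule.
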